**Figure 2 F2:**
[figure not shown]
**SMARTSteps-PLUS protocol for automated telephone self-management (ATSM) with enhanced medication adherence and intensification counseling**.

1. Patients who indicated in response to weekly ATSM queries that they missed 3-7 days of medications in the last week.

2. Patients with a 15-day to 6-month gap in refilling specific cardiometabolic prescriptions: oral hypoglycemic, insulin, anti-hypertensives (including ACE inhibitors and angiotension-receptor blockers), cholesterol-lowering medications, or glucose testing strips (for patients receiving insulin or sulfonylureas), based on pharmacy claims data. We chose a lower limit of 15-days to account for potential delays in SFHP receipt of pharmacy claims and an upper limit of 6 months in case healthcare providers actively discontinued these medications.

3. Patients with suboptimal achievement of cardiometabolic goals [43]:

• Systolic blood pressure ≥ 130 mmHg at last recorded check or no measurement in clinical registry within preceding 6 months

• Diastolic blood pressure ≥ 80 mmHg at last recorded check or no measurement in clinical registry within preceding 6 months

• Hemoglobin A1c (HbA1c) > 7.0% on last measurement or no measurement in clinical registry within preceding 6 months

• Low-density lipoprotein (LDL) > 100 mg/dL on last measurement or no measurement in clinical registry within preceding 12 months

• Urinary albumin/creatinine > 30 mcg/mg for patients who were not prescribed or late to refill an ACE inhibitor or angiotensin-receptor blocker

An individual SMARTSteps-PLUS participant could fall into none, one, or more than one of these groups at any given time. SFHP queried the pharmacy claims and clinical registry data monthly to provide health coaches with a list of SMARTSteps-PLUS participants to be called.

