For patients with evidence of non-adherence, SFHP health coaches were trained with specific written protocols and scripts to promote self-disclosure of medication non-adherence and troubleshoot barriers such as confusion about doses or frequency of medications, forgetfulness, concerns about side effects, or health beliefs (see Additional File 1). For patients who had not had cardiometabolic measurements within guideline-concordant timeframes, health coaches counseled patients about the reasons for these measures, encouraged them to talk with their providers, and notified PCPs of patients willing to obtain these tests. For patients with suboptimal achievement of treatment goals, health coaches were trained to counsel patients about their blood pressure or lab values and assess their willingness to discuss with their PCPs the possibility of taking more medication. Health coaches also encouraged patients to undergo potential lifestyle changes. Based on their discussions, health coaches engaged patients in collaborative goal-setting and action planning [20,35]. Health coaches then notified the clinic contacts and/or PCPs about interactions with any patients who needed laboratory or blood pressure assessments, reported barriers to medication adherence, or indicated a willingness to discuss medication intensification.

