**Secondary outcome variables**	

Diabetes self-management behaviors	Summary of Diabetes Self-Care Activities (SDSCA) measure [52]

Self-reported medication adherence	Summary of Diabetes Self-Care Activities (SDSCA) measure [52]

Diabetes self-efficacy	Patient self-management scale derived from questionnaire used in the Diabetes Quality Improvement Project [54]

Patient-centeredness of care	Patient Assessment of Care for Chronic Conditions (PACIC) [55] Interpersonal processes of care (IPC) [56]

Glycemic control	Hemoglobin A1c

Blood pressure control	Systolic and diastolic blood pressure

Cholesterol control	Low-density lipoprotein

Quality of care	Proportions receiving hemoglobin A1c and blood pressure measurement within 6 months [43,47]

	Proportions receiving LDL and microalbumin/creatinine measurement within 12 months [43,47]

	Proportion receiving retinal examination within 12 months [43,47]

	Proportion receiving influenza and pneumococcal vaccination [43,47]

Utilization	Emergency department Hospitalization

For participants consenting to the UCSF evaluation trial, measures of all primary and secondary patient-reported outcomes were derived from structured interviews conducted in English, Spanish or Cantonese. For Spanish and Cantonese interviews, survey questions were translated and back-translated in their respective languages. Interviews were administered using computer-assisted telephone interview (CATI) software or paper survey, with responses later entered into the CATI-created database. Consenting participants completed baseline interviews within 2 weeks of being randomized, prior to the first ATSM call. SMARTSteps-ONLY and SMARTSteps-PLUS participants completed the 6-month follow-up interviews after the conclusion of their ATSM intervention, and wait-list participants completed the 6-month follow-up interviews before the start of their ATSM calls. Wait-list groups received an additional 6-month follow-up interview (12 months after enrollment) after completion of intervention period. Participants received a $50 gift card for a pharmacy store at the completion of each interview.

For all eligible SFHP members, we collected socio-demographic variables and cardiometabolic outcomes data using monthly downloads of SFHP claims data and CHNSF clinical registry data. At the conclusion of the project, we will obtain SFHP administrative and claims data for utilization outcomes.

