#### Cardiometabolic Outcomes

These secondary outcomes will be analyzed on the larger set of SFHP participants randomized in the trial (N = 362), regardless of whether or not they participated in the evaluation interviews. Cardiometabolic outcomes include measures of HbA1C, LDL, and blood pressure obtained by clinical providers. Data will be derived from CHNSF electronic health record, the clinical registry database, and paper chart review. Values will be used at baseline only if obtained within one year before program enrollment. Follow-up laboratory and blood pressure values will be included only if obtained within 90 days before or after the 6-month and 12-month follow-up dates.

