#### Sample size calculations

Sample size calculations were based on comparison of primary outcomes for the combined intervention groups (SMARTSteps-ONLY and SMARTSteps-PLUS) with the combined wait-list control groups. Based on an eligible population of approximately 500 SFHP members, we anticipated recruitment of 260 participants to intervention and control with a 10% drop-out or loss to follow-up rate at 6 months. Using a two-tailed test, we calculated that we would have 80% power to detect a standardized effect size (SE) of 0.35 in the primary outcome of SF-12 scores, comparing the combined intervention groups with the combined wait-list groups. In the prior RCT, we observed standardized effect sizes in this range [33].

We estimated that over the course of the two-year observation period, approximately 20% of enrolled participants would have insufficient data for secondary cardiometabolic outcomes to be included in these analyses. Under this assumption, we would have 80% power to detect a difference in HbA1c of 0.51% (SE 0.28) when comparing wait-list vs. combined ATSM interventions participants. This effect size is intermediate between that estimated to be the effect on glycemic control of diabetes disease management programs that involve team changes (-0.3% HbA1c improvement) and those that involve medication intensification strategies (-0.6%) [57].

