The results of this evaluation trial, when completed, must be interpreted within the following limitations. First, SFHP's phone-based population recruitment targeted different languages over time due to enrollment worker availability, with greater emphasis on Cantonese-speaking populations earlier. Thus, potential differences in intervention impact by language may relate to changes in project implementation over time. Second, because SFHP does not have medication prescribing authority for its members or authority to document within participants' medical records, the interventions will not be fully-integrated into care delivery in the context of participants' medical homes; this may limit the effectiveness of the intervention, particularly the SMARTSteps-PLUS medication intensification arm. Finally, because data for cardiometabolic outcomes relies on collection through routine medical care rather than scheduled study visits, we may not be powered to detect a modest impact of the intervention on glycemic or blood pressure control.

Improving health communication through the use of tailored, proactive HIT is one scalable vehicle to improve chronic disease care for vulnerable populations [32,33]. Focusing on improving the processes of care for vulnerable populations in under-resourced safety net settings through the application of evidence-based or evidence-informed HIT tools can have far-reaching implications for bridging the clinical care-public health divide, not only for diabetes, but for other chronic conditions and for preventive services [27]. The SMARTSteps outcomes will provide evidence regarding the real-world implementation of ATSM within a Medicaid managed care plan and provide insight into translating and scaling up HIT interventions for linguistically and culturally diverse vulnerable populations with chronic disease.

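### The HbA1c, LDL and blood pressure comparisons are open to arm-dependent selection: only in-window routine values count, and only SMARTSteps-PLUS prompts overdue measurements

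*Protocol article*

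**What the plan says.** **Which values count.** Under Cardiometabolic Outcomes: "Follow-up laboratory and blood pressure values will be included only if obtained within 90 days before or after the 6-month and 12-month follow-up dates". For baseline: "Values will be used at baseline only if obtained within one year before program enrollment". The Discussion notes that "data for cardiometabolic outcomes relies on collection through routine medical care rather than scheduled study visits". Sample size calculations expects that "approximately 20% of enrolled participants would have insufficient data for secondary cardiometabolic outcomes to be included in these analyses".

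**What differs by arm.** The SMARTSteps-PLUS triggers under Figure 2 include "Hemoglobin A1c (HbA1c) > 7.0% on last measurement or no measurement in clinical registry within preceding 6 months", with similar rules for blood pressure (6 months) and LDL (12 months). The registry is queried monthly for PLUS participants only. For those without a timely measurement, coaches explain why it matters, encourage contact with the provider, and "notified PCPs of patients willing to obtain these tests". SMARTSteps-ONLY has no registry-driven trigger. Wait-list patients keep the plan's existing reminders and incentives, which cover laboratory testing (Wait-list Control).

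**Testing as an outcome.** Table 1 lists "Proportions receiving hemoglobin A1c and blood pressure measurement within 6 months", and corresponding 12-month proportions for LDL and microalbumin.

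**Analysis.** Data analyses sets out two methods: a regression of 6-month changes adjusted for the baseline value, and a maximum-likelihood repeated-measures model. Both are also to be used for ONLY versus PLUS. All analyses are called intent-to-treat (Study integrity).

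**Stated limitation.** On the consequence of relying on routine-care data, the Discussion says only that "we may not be powered to detect a modest impact of the intervention on glycemic or blood pressure control".

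**The concern.** Randomisation protects a comparison of everyone randomised. It does not protect a comparison of those who happened to be measured, if the arm can influence who is measured. Here one arm contains a process intended to produce measurements in patients who lack them, and the plan lists measurement as something the intervention may change. If that process works, the set analysed for HbA1c, LDL and blood pressure differs in composition between arms. The intent-to-treat label does not supply values for unmeasured participants.

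At stake is how the cardiometabolic results are read, above all PLUS against ONLY, where the registry-driven prompt is one of the features that separate the arms. A null, favourable or unfavourable result could partly reflect who was tested.

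**Working it through.** **1. Can the arm affect inclusion?** The baseline rule looks back from enrolment, so the arm cannot affect it. The follow-up rule depends on a routine test taken after randomisation. In PLUS, a missing test triggers coaching and, for willing patients, a notice to the provider. A last value above goal also triggers coaching, so provider contact in PLUS depends partly on post-baseline values. Neither registry trigger applies in ONLY or during the wait-list period. The route from arm to inclusion is in the text; its strength is not.

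**2. The plan's own figures.** (Two-sided alpha 0.05 assumed, 80% power, equal groups.) Detectable standardised difference = (1.96 + 0.84) x sqrt(4/N).
- Planned: 80% of 500 eligible = 400, giving 0.280. This matches the stated 0.28 (0.51%, implied SD 0.51/0.28 = 1.82).
- Updated (Recruitment): 348 x 0.8 = 278. The stated 0.37% then needs an SD of 1.10. The tabulated baseline SD of 1.6 would give 0.54%, so 0.37% presumably reflects a change-score or baseline-adjusted SD (correlation about 0.73-0.76).

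Both figures apply one common 20% loss and so allow for no difference in observation between arms.

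**3. Two-group illustration (all inputs assumed, no true effect).** A share u of participants has little contact with care, and their HbA1c change is g points worse. Half of them are measured in the comparison arm and a share r in PLUS; 90% of everyone else is measured in both arms. The false difference is g times the difference in the low-contact share among those measured.
- u = 0.3, r = 0.8, g = 0.5: 0.24/0.87 - 0.15/0.78 = 0.276 - 0.192 = 0.084; x 0.5 = 0.04.
- Over u = 0.2-0.4, r = 0.65-0.8 and g = 0.3-1.0: 0.01 to 0.10 points.

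**4. Baseline-adjusted regression (simulation, no true effect).** Follow-up = 7.7 + 0.75 x (baseline - 7.7) + error. Baseline SD is 1.6 (Table 2); error SD is 1.1. The chance of being observed follows a logistic model; slopes are per SD of the driver (comparison arm / PLUS).

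| Missingness depends on | Observed, comparison / PLUS | Slopes | Bias in HbA1c points |
|---|---|---|---|
| nothing | 70% / 90% | none | 0.00 |
| baseline HbA1c only | 70% / 90% | -0.5 / -0.5; -0.5 / 0; -1 / 0 | 0.00 |
| unexplained follow-up value | 80% / 80% | -0.5 / -0.5 | 0.00 |
| unexplained follow-up value | 75% / 85% | -0.5 / -0.25 | 0.09 |
| unexplained follow-up value | 70% / 90% | -0.5 / -0.5 | 0.10 |
| unexplained follow-up value | 70% / 90% | -0.5 / 0 | 0.16 |
| unexplained follow-up value | 70% / 90% | -1 / 0 | 0.28 |

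These slopes make patients with higher values less likely to be tested, so PLUS looks worse. Reversing the slopes reverses the sign.

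**5. Which comparison, and which yardstick?** PLUS is about half of the intervention group, so pooling gives roughly 0.09/2 = 0.04 to 0.28/2 = 0.14 at the biased end. The 0.37% yardstick suits only that pooled comparison. For immediate PLUS versus immediate ONLY, about half the sample (182 of 362 went directly to intervention), the same inputs give about 0.37 x 1.41 = 0.52%.

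**The case against.** Several counter-arguments stand.

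- **Bias is not demonstrated.** A reader might infer that the comparison is biased, and that it hides a benefit or creates apparent harm. The article supports neither: it gives no testing rates by arm and nothing to show that untested patients have worse values. If well-controlled patients are the ones tested less, the sign reverses.
- **The comparison arms are not without prompts.** Wait-list patients keep testing reminders and incentives. ONLY participants are asked about preventive services, and their coaches contact clinics about access problems. The 6-month window runs from about month 3 to month 9, while wait-list patients cross over at month 6, so those waiting for PLUS receive the prompts inside that window. It would be wrong to say that all wait-list patients stay unprompted.
- **Few were long untested at enrolment.** 348 of 362 (96%) had a baseline HbA1c. The share overdue by the 6-month PLUS trigger is not given.
- **A likelihood model is already planned**, with predictors of dropout as possible covariates, and testing proportions are already outcomes. The plan does not rest on the in-window regression alone.
- **The 20% is a planning assumption**, not an exclusion rule, and imputation detail commonly belongs in an analysis plan.

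These points limit the size and certainty of the problem. They do not remove it: the inclusion rule, the PLUS-only prompt and the power-only limitation are all fixed in this article. Under missing at random the likelihood model is adequate; under the mechanism in the lower rows of the table it is not.

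**Conclusion.** The cardiometabolic comparisons are open to arm-dependent selection, and the article treats reliance on routine data as a power limit only. PLUS versus ONLY is most exposed. ATSM versus wait-list is affected in diluted form, for three reasons: about half of the intervention group is PLUS, wait-list patients keep reminders, and those waiting for PLUS are prompted from month 6.

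Under the assumptions shown, the baseline-adjusted HbA1c bias for PLUS against a comparison arm lies between 0 and about 0.1-0.3 points, and about half that when pooled. The upper end needs both a clear gap in testing between arms and missingness that baseline does not explain. The documents establish neither.

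Only secondary outcomes are concerned. SF-12 and bed days come from interviews and are untouched. The change is worth making because it is cheap, not because an error has been shown.

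**What to change.** - Report the proportion with an in-window value, by arm, beside each HbA1c, LDL and blood pressure result.
- For these outcomes, make the planned likelihood-based repeated-measures model the main analysis in place of the in-window-only regression. Use every dated registry value for all 362, classified by exposure on its date, with an overdue-at-enrolment covariate. Both registry triggers act on recorded values and dates, so bringing these into the model makes missing at random more plausible.
- Add a delta-adjusted (missing-not-at-random) sensitivity analysis. Which patients agree to testing and attend may depend on things the registry does not hold, and the likelihood model does not correct for that.
- Add an analysis restricted to participants not overdue at enrolment.
- State in the Discussion that reliance on routine-care data is a possible source of bias as well as a limit on power.

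The cost is extra analysis work on registry data already downloaded monthly, with no new collection and no change to the intervention. The downside is a missing-at-random assumption in the main model, which the sensitivity analyses probe but cannot settle.

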### Study integrity

The study design conforms to CONSORT statement recommendations for randomized trials of non-pharmacologic treatment [48]. Randomization to intervention groups was conducted by SFHP before assessment of willingness to participate in UCSF evaluation interviews to permit analysis of primary outcomes. Intervention arm assignment was conducted using a 4 × 4 blocked randomized design, with the participant as the unit of randomization. This randomization was completed for each of the three study languages. Research assistants administering the evaluation interviews were blinded to group allocation. The intervention protocol is documented and filed on secure servers. Data generated during ATSM and health coach calls is stored in the ATSM and SFHP database systems, respectively. All analyses will be intent-to-treat.

### Measurement

#### Data Collection

Table 1 lists study outcomes.

**Table 1 T1:** Outcomes for SMARTSteps, a quasi-experimental evaluation trial of a language-concordant automated telephone diabetes self-management health plan intervention

Variable	Instrument
**Primary outcome variables**	

Functional status	SF-12 [51] Days confined to bed due to illness

**Secondary outcome variables**	

Diabetes self-management behaviors	Summary of Diabetes Self-Care Activities (SDSCA) measure [52]

Self-reported medication adherence	Summary of Diabetes Self-Care Activities (SDSCA) measure [52]

Diabetes self-efficacy	Patient self-management scale derived from questionnaire used in the Diabetes Quality Improvement Project [54]

Patient-centeredness of care	Patient Assessment of Care for Chronic Conditions (PACIC) [55] Interpersonal processes of care (IPC) [56]

Glycemic control	Hemoglobin A1c

Blood pressure control	Systolic and diastolic blood pressure

Cholesterol control	Low-density lipoprotein

Quality of care	Proportions receiving hemoglobin A1c and blood pressure measurement within 6 months [43,47]

	Proportions receiving LDL and microalbumin/creatinine measurement within 12 months [43,47]

	Proportion receiving retinal examination within 12 months [43,47]

	Proportion receiving influenza and pneumococcal vaccination [43,47]

Utilization	Emergency department Hospitalization

For participants consenting to the UCSF evaluation trial, measures of all primary and secondary patient-reported outcomes were derived from structured interviews conducted in English, Spanish or Cantonese. For Spanish and Cantonese interviews, survey questions were translated and back-translated in their respective languages. Interviews were administered using computer-assisted telephone interview (CATI) software or paper survey, with responses later entered into the CATI-created database. Consenting participants completed baseline interviews within 2 weeks of being randomized, prior to the first ATSM call. SMARTSteps-ONLY and SMARTSteps-PLUS participants completed the 6-month follow-up interviews after the conclusion of their ATSM intervention, and wait-list participants completed the 6-month follow-up interviews before the start of their ATSM calls. Wait-list groups received an additional 6-month follow-up interview (12 months after enrollment) after completion of intervention period. Participants received a $50 gift card for a pharmacy store at the completion of each interview.

For all eligible SFHP members, we collected socio-demographic variables and cardiometabolic outcomes data using monthly downloads of SFHP claims data and CHNSF clinical registry data. At the conclusion of the project, we will obtain SFHP administrative and claims data for utilization outcomes.

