**Methods/Design:**

This controlled quasi-experimental trial used a wait-list variant of a stepped wedge design to enroll 362 adult health plan members with diabetes who speak English, Cantonese, or Spanish and receive care at 4 publicly-funded clinics. Through language-stratified randomization, participants were assigned to four intervention statuses: SMARTSteps-ONLY, SMARTSteps-PLUS, or wait-list for either intervention. In addition to usual primary care, intervention participants received 27 weekly calls in their preferred language with rotating queries and response-triggered education about self-care, medication adherence, safety concerns, psychological issues, and preventive services. Health coaches from the health plan called patients with out-of-range responses for collaborative goal setting and action planning. SMARTSteps-PLUS also included health coach calls to promote medication activation, adherence and intensification, if triggered by ATSM-reported non-adherence, refill non-adherence from pharmacy claims, or suboptimal cardiometabolic indicators. Wait-list patients crossed-over to SMARTSteps-ONLY or -PLUS at 6 months. For participants who agreed to structured telephone interviews at baseline and 6 months (n = 252), primary outcomes will be changes in quality of life and functional status with secondary outcomes of 6-month changes in self-management behaviors/efficacy and patient-centered processes of care. We will also evaluate 6-month changes in cardiometabolic (HbA1c, blood pressure, and LDL) and utilization indicators for all participants.

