## Methods/Design

### Study aims

Among ethnically and linguistically diverse persons with diabetes receiving care in a primary care safety net system:

*Primary Aim: *To investigate differences in 6-month changes in patient-centered outcomes including quality of life and functional status (SF-12 and number of days spent in bed due to illness), comparing patients exposed to ATSM with wait-list controls and comparing patients exposed to ATSM (SMARTSteps-ONLY) with ATSM augmented by medication adherence and intensification (SMARTSteps-PLUS).

*Secondary Aims: *To investigate differences in 6-month changes in diabetes self-management behaviors and self-efficacy, patient-centered processes of care, cardiometabolic outcomes (HbA1c, blood pressure, and LDL), receipt of recommended health services, and healthcare utilization, comparing patients exposed to ATSM with wait-list controls and comparing patients exposed to ATSM (SMARTSteps-ONLY) with ATSM augmented by medication adherence and intensification (SMARTSteps-PLUS).

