#### Wait-list Control

Those randomized to the wait-list continued to receive usual care through their clinics, as well as all existing SFHP benefits (reminders and incentives for receipt of recommended health services, including laboratory testing, eye and foot examination, and influenza vaccination) [43,47]. At the end of the 6-month wait-list period, each participant "crossed-over" to begin SMARTSteps-ONLY or SMARTSteps-PLUS, depending on initial randomization arm.

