#### SMARTSteps-ONLY

Participants randomized to SMARTSteps-ONLY received the ATSM intervention within 2 weeks. Developed with extensive input from patients to be sensitive to literacy, language, and culture in the target populations [32], this ATSM system provided 27 weeks of 8-12 minute weekly calls in English, Cantonese, or Spanish. Patients specified the weekday and time convenient for their schedules or called toll-free into the system if they missed their scheduled call. The content consisted of rotating sets of queries about self-care (such as diet, exercise, and medication adherence), psychosocial issues (such as depressive symptoms), and access to preventive services (such as eye care). Patients responded via touch-tone commands, and based on their answers, patients heard automated health education messages in the form of narratives.

Patients answering "out-of-range" on an item or selecting a "call back" option received a telephone call within 3 days from a language-concordant SFHP health coach. This system was designed to promote health coach efficiency and effectiveness by focusing outreach calls to patients needing further support based on ATSM responses. Health coaches provided education and engaged in collaborative goal-setting to form patient-centered action plans, a core process for self-management support by which patients set short-term goals to improve their self-management [20,35].

SFHP used a health coach for responding to ATSM triggers, rather than a nurse practitioner care manager as was done in the IDEALL trial [33]. Health coaches - SFHP employees without a medical background or postgraduate training - conducted phone calls under the supervision of a registered nurse care manager. SFHP registered nurse supervisors and UCSF study physicians taught health coaches about diabetes and trained them in behavior change counseling and overcoming barriers to health communication. UCSF staff also guided the development of written protocols and scripts to respond to potential ATSM call triggers, such as assessing hypoglycemia symptoms or causes.

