### Data analyses

We will assess the similarity of baseline characteristics between study arms using t-tests, chi-square tests, and Fisher's exact tests. We will control for any significant differences in baseline characteristics in analyses of all primary and secondary outcomes.

For each outcome, we will compare differences between study arms in 6-month changes using intent-to-treat analyses. Because this study is a quasi-experimental evaluation trial with a wait-list variant of a stepped wedge design, analyses of outcome changes will be conducted with two distinct methodologies. The first method will involve analyzing the data as if the trial was a standard intervention versus control study, comparing all participants who were randomized to the ATSM intervention (either SMARTSteps-ONLY or SMARTSteps-PLUS) versus all participants randomized to the wait-list control groups. We will use linear regression for continuous variables, logistic regression for dichotomous variables, and negative binomial models for the outcome variable of number of bed days because of its non-parametric data distribution. We will include as model covariates the baseline value of outcome variables and any socio-demographic or medical variables that may have differed by chance among the groups.

The second method will take advantage of the wait-list variant, stepped wedge design with study cross-over of participants from control to intervention [40]. It will employ a repeated measures analysis using maximum likelihood to fit the models. Because discrete external events may coincide with the time that participants cross-over from control to intervention and thereby possibly confound the within-group comparisons from the wait-list control group, secular effects in the wait-list group will be modeled first to see if a specific spline to capture non-linearities analysis is needed or if a simple linear trend exists, simplifying the analysis. Other possible covariates in the model may be calendar time, actual time of intervention exposure, and predictors of dropping out of study.

To explore the added value of the medication activation arm, both the first and second methods above will also be used to compare SMARTSteps-ONLY versus SMARTSteps-PLUS in all primary and secondary outcomes.

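### Three quality-of-care outcomes (LDL testing, microalbumin/creatinine testing, retinal examination) use a 12-month window that does not fit the 6-month randomised comparison with wait-list, costing an unknown amount of sensitivity

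*Protocol article*

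**What the plan says.** Table 1 of the protocol article lists, under quality of care, "Proportions receiving LDL and microalbumin/creatinine measurement within 12 months" and "Proportion receiving retinal examination within 12 months". The same block gives a shorter window to two other services: "Proportions receiving hemoglobin A1c and blood pressure measurement within 6 months".

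The secondary aims (Study aims) place these outcomes among the 6-month changes to be studied: "receipt of recommended health services, and healthcare utilization, comparing patients exposed to ATSM with wait-list controls". Data analyses applies one contrast throughout: "For each outcome, we will compare differences between study arms in 6-month changes using intent-to-treat analyses".

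The control condition is short. The abstract states that "Wait-list patients crossed-over to SMARTSteps-ONLY or -PLUS at 6 months", and the Wait-list Control section puts the switch "At the end of the 6-month wait-list period". The intervention is of similar length: "this ATSM system provided 27 weeks of 8-12 minute weekly calls".

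Care Delivery Processes and Utilization adds that frequencies follow the guideline. The article gives no date on which the 12-month window ends.

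**The concern.** The outcome window is twice as long as the period in which the arms differ by randomisation. At month 6, a patient served in the half-year before randomisation is already counted as having received the service. Nothing the programme does can change that value. At month 12, both arms have had one intervention period, so the contrast with untreated controls has gone.

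At stake is whether a null result on these three indicators could be read as no effect on care delivery. HbA1c and blood pressure testing, with their 6-month window, do not have the problem. The primary outcomes (SF-12 and bed days) are not touched.

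**Working it through.** The article gives no expected rate or power for these proportions, so there is no stated figure to reproduce.

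**Window arithmetic (document figures only).** Let a 12-month window end at month t, with t between 6 and 12.
- Months before randomisation: 12 − t.
- Months after controls cross over: t − 6.
- Total outside the randomised period: (12 − t) + (t − 6) = 6, so 6/12 = 50% wherever the window ends.
- t = 6: months −6 to +6, half before randomisation in both arms.
- t = 12: months 0 to 12, half of the wait-list window on the intervention.

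The 12-month windows ending at month 0 and month 6 also share months −6 to 0, which weakens a change score.

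**Inputs for the illustration.** 182 patients randomised to intervention and 180 to wait-list (Figure 1 legend). Assumed, not from the article: receipt p per untreated half-year, independence between half-years, and an overall effect of 15 points in the 6 months after randomisation. Two-sided α = 0.05; power = Φ[(d − 1.96·se₀)/se₁], with se₀ pooled and se₁ unpooled.

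Worked case, 6-month window, p = 0.45: 0.45 v 0.60; pooled rate (81 + 109.2)/362 = 0.525; se₀ = 0.0525; se₁ = 0.0519; power = Φ[(0.15 − 0.1029)/0.0519] = 0.82.

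**Model A: the effect is uniform**, so patients served recently respond as much as the rest. At month 6 the 12-month indicator is 1 − (1 − p)² in controls and 1 − (1 − p)(1 − p − 0.15) in the intervention arm.

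| p | 12-month indicator | Difference | Power, 12-month | Power, all patients, 6-month |
|---|---|---|---|---|
| 0.30 | 0.510 v 0.615 | 0.105 | 0.52 | 0.84 |
| 0.45 | 0.6975 v 0.780 | 0.0825 | 0.43 | 0.82 |
| 0.60 | 0.840 v 0.900 | 0.060 | 0.40 | 0.87 |

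**Model B: the same 15 points overall, falling only on patients not served in months −6 to 0.** Patients already served add nothing to the difference in either window, so the 12-month difference stays at 0.15.

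| p | 12-month indicator | Difference | Power, 12-month | Power, all patients, 6-month |
|---|---|---|---|---|
| 0.30 | 0.510 v 0.660 | 0.15 | 0.83 | 0.84 |
| 0.45 | 0.6975 v 0.8475 | 0.15 | 0.93 | 0.82 |

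**Restricting to patients with no record in months −6 to 0**, p = 0.45: 180 × 0.55 = 99 and 182 × 0.55 ≈ 100 patients.
- Model A: 0.45 v 0.60, power 0.56 (12-month indicator: 0.43).
- Model B: effect among these patients 0.15/0.55 = 0.273, so 0.45 v 0.723, power 0.98 (12-month indicator: 0.93).

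For these patients, receipt in the 12 months to month 6 and receipt since randomisation are the same event. The restriction removes only patients whose 12-month value could not change.

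**Month 12.** Write q₀ for untreated and q₁ for treated half-year receipt. The intervention arm has 1 − (1 − q₁)(1 − q₀) and the wait-list 1 − (1 − q₀)(1 − q₁). The expected difference is 0 if the effect is confined to the intervention period and there is no secular trend.

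**The case against.** **The programme may act mainly on patients who are due.** This is the strongest point. In SMARTSteps-PLUS the testing trigger for LDL is the absence of a registry value in the past 12 months, and coaches counsel patients whose measurements are out of date. That resembles Model B, where the 12-month indicator loses little or nothing against an unrestricted 6-month window. A reader might infer that the effect is diluted by construction, that power falls from 82% to 43%, and that a real effect is likely to be missed. The documents do not support this: those figures need a uniform effect and independent half-years. The objection is not complete either. That trigger covers LDL only and PLUS only, the microalbumin trigger depends on the measured value, and automated queries on preventive services such as eye care go to both versions. The mechanism is mixed and its balance is not known.

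**Guideline concordance is a legitimate measure.** It is, and simple receipt in months 0 to 6 would score as a failure a patient served shortly before enrolment. This stands against an unrestricted 6-month outcome. It does not stand against one restricted to, or stratified by, patients without recent service.

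**Baseline adjustment is already planned.** Data analyses includes the baseline value as a covariate. But 12-month baseline status gives the same value to a patient served at month −3, who is fixed as served at month 6, and one served at month −9, who can still respond.

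**The end date may be set in a fuller document.** Possibly, but no end date removes the mismatch.

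**The ONLY versus PLUS comparison is not affected in this way.** This stands. Wait-list patients cross over to their assigned version, so a window over months 0 to 12 lies wholly after randomisation for that contrast.

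**The second analysis method models the cross-over.** It does, but a single 12-month value still mixes exposed and unexposed time.

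**Conclusion.** The mismatch is real and follows from the article's own timing: half of any 12-month window containing the randomised period lies outside it. For intervention versus wait-list, these three indicators lose some sensitivity. At month 6 the pre-randomisation half is balanced in expectation, so false-positive error is not inflated, and nobody should infer bias in favour of the programme.

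The size cannot be fixed from the article. At an assumed p = 0.45 and 15 points, the 12-month indicator at month 6 has power between 0.43 (uniform effect) and 0.93 (effect only on patients not recently served). Under both models the restricted post-randomisation analysis does better: 0.56 and 0.98. That comparison, rather than any single power loss, is the reason to change. The matter is confined to three secondary indicators but is cheap to put right.

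**What to change.** For the intervention versus wait-list comparison of LDL testing, microalbumin/creatinine testing and retinal examination:

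- Define the outcome as a service dated after randomisation and up to the 6-month date, and for wait-list patients before the first ATSM call.
- Restrict the analysis to patients with no record of that service in the 6 months before randomisation, or stratify by that status. Stratifying keeps everyone in the analysis, which matters if the effect is nearer uniform: at p = 0.45 the restricted analysis then has power 0.56, against 0.82 for all patients over 6 months.
- Report the 12-month guideline indicator alongside as a quality-of-care figure, with the end date of its window stated.

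The ONLY versus PLUS comparison need not change on this account.

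The cost is re-coding of dated claims and registry records already held, with no new data collection. The downside is that the guideline metric is no longer the main between-arm display for these three indicators.
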